#### **14.9.2.5. Exploratory Efficacy Analyses**

Sensitivity analyses on the primary efficacy variable may be conducted using the alternate imputation methods such Baseline Observation Carried Forward (BOCF) or Mixed-Model Repeated Measures (MMRM) imputed data. The data will then be analyzed using the same ANCOVA model that was used to analyze the primary efficacy variable. This will be done for the ITT population (Full analysis) only.

Adding the treatment-by-site (pooled site) interaction term to the ANCOVA model that was used in the analysis of the primary efficacy variable. If significant at the 0.10 level, summary and inferential statistics will be presented for each (pooled) site. This will be done for the ITT population (Full analysis) only.

Subgroup analyses on selected efficacy variables may be conducted using the ITT (Full analysis) population if deemed necessary.

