## 14.2. Sample Size and Accrual

The sample size is based on the average LPS computed via PSG assessments from nights 1 and 8. Based on a t-test to detect a 15 minute difference between VEC-162 treated patients and placebo patients, and assuming a common standard deviation of 30 minutes, a sample size of 86 patients per treatment arm is needed in order to have 90% power with a two-sided alpha of 0.05. The standard deviation is based on data found in literature. Considering a 1:1:1 randomization between VEC-162 20mg, VEC-162 50mg and placebo, and a 20% drop-out rate, a total of 324 patients (108 per arm) will be needed.

A re-estimation of the sample size will be done through an adjusted one-sample variance procedure. In this procedure, a blinded variance estimation is obtained by adjusting the one-sample variance of the pooled sample.

Let  $N$  and  $VAR$  be the respective preliminary sample size and variance originally estimated (as per above). Let  $N(s)$  and  $VAR(s)$  be the respective sample size and variance of the pooled blinded sample at this sample-size re-assessment look. Then according to Zucker et al. (13), the following estimation of the variance ( $VAR(adj)$ ) will be used to generate an adjusted sample size  $N(adj)$ ;

$$VAR(adj) = VAR(s) - N(s) D^2 / 2(2N(s)-1),$$

where  $D$  is equal to a 15 point change from baseline

$N(adj)$  will then be generated using a two-group t-test procedure with a 0.05 two-sided significance level and the variance  $VAR(adj)$ .

Since this sample size re-assessment is not intended to stop the trial early due to efficacy but only to provide a variance re-estimation and a sample size recalculation, then after the recruitment of the first  $n(s)$  patients,

- if  $N(adj) \leq N$ , then a further  $N-N(s)$  patients will have to be recruited until the initially planned sample size  $N$  is reached.
- Otherwise if  $N(adj) > N$ , then a further  $N(adj)-N(s)$  patients will have to be recruited.

As the procedure does not require unblinding of the treatment code during the ongoing trial nor produce any estimation of a treatment effect hypothesis testing, then no adjustment to control the nominal significance level is required.

The required sample size could also be adjusted if the drop-out rate differs from the estimated drop-out rate. This change would be made via a protocol amendment.

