## 14.4. Patient Populations for Analysis

The following analysis populations will be defined for this study:

**Randomized:** will include any patient randomized into the study. This population can be referred to as the Intent-to-Treat population.

**Full Analysis:** will include any patient randomized into the study that receive a dose of study drug and have post-baseline polysomnography data. This analysis population may also be referred to as the modified Intent-To-Treat population.

**Safety:** Any patient randomized into the study that receives a dose of study drug.

**Per-Protocol:** Any patient who is randomized and receives the protocol required study drug exposure and required protocol processing, e.g., patients who undergo all five overnight visits [Nights 1, 8, 22, 29 ( $\pm 2$  days) and 36] in which PSG is assessed.

Primary analyses of efficacy endpoints (primary and secondary) will be performed on the Full Analysis Set. Additionally, these analyses will be repeated on the Per-Protocol set. Safety summaries will be based on Safety set. Patient characteristics will be presented for all patients randomized.

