##### **14.9.2.1. General Data Analysis Considerations**

###### **Imputation of missing data**

For the average PSG parameter values calculated as an average over 2 nights (Night 1 and 8 or Nights 22 and 29), if one of the 2 nights entering in the calculation of the average value is missing, then it will be imputed using the non-missing night value, e.g. if Night 1 is missing then it will be imputed using the Night 8 value and if Night 8 is missing, it will be imputed using the Night 1 value. If both post-baseline values are missing then the average value for this PSG parameter will be imputed using the baseline value only (Baseline Observation Carried Forward - BOCF).

The observed data will otherwise be used in the analyses.

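### The optional MMRM sensitivity analysis is set up as imputation followed by the ordinary ANCOVA, which on its natural reading makes its standard error somewhat too small

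*Protocol*

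**What the plan says.** The primary variable is LPS averaged over Nights 1 and 8. Protocol section 14.9.2.1 fixes the primary missing-data rule: "if one of the 2 nights entering in the calculation of the average value is missing, then it will be imputed using the non-missing night". For a patient with neither night, "If both post-baseline values are missing then the average value for this PSG parameter will be imputed using the baseline value only".

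Section 14.9.2.5, headed as exploratory, then offers a check on that rule: "Sensitivity analyses on the primary efficacy variable may be conducted using the alternate imputation methods such Baseline Observation Carried Forward (BOCF) or Mixed-Model Repeated" Measures imputed data. The step from imputation to analysis reads: "Mixed-Model Repeated Measures (MMRM) imputed data. The data will then be analyzed using the same ANCOVA model" as for the primary variable. No repeated draws, combining rule or variance correction is mentioned.

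The Full Analysis set (section 14.4) "will include any patient randomized into the study that receive a dose of study drug and have post-baseline polysomnography data". Section 14.1 leaves full methodological detail to the SAP and lets statistical methods change before database lock without a protocol amendment.

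**The concern.** MMRM is a likelihood analysis of incomplete repeated measures. Its standard errors already reflect the nights that were not recorded. The protocol uses it instead to produce values, then passes the completed data to the primary ANCOVA.

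A model prediction has no residual scatter, and the coefficients behind it are themselves estimated. An ANCOVA that treats it as a measurement makes two errors: its residual variance is too small, and it counts more information than was collected. Both push the p-value down.

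The point matters because of the purpose of the analysis. MMRM is the only model-based alternative named. The other one, BOCF, is already part of the primary rule when both nights are missing. A robustness check should not lean toward agreeing with a significant primary result.

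**Working it through.** **The protocol's own figure.** Section 14.2 rests on this: "Based on a t-test to detect a 15 minute difference between VEC-162 treated patients and placebo patients", with SD 30, two-sided alpha 0.05 and 90% power. The normal approximation is 2(1.96 + 1.2816)² × 30²/15² = 84.1, so 85 per arm. The exact t-test has power 0.8999 at 85 and 0.9032 at 86, so 86 is right. Then 86/0.80 = 107.5, so 108 per arm and 324 in total. These figures reproduce, and nothing below changes them.

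**Inputs that the protocol does not give (assumptions).**
- Share m of patients with Night 8 missing: 4%, 5%, 10% and 20%. The 20% figure puts the whole drop-out allowance before Night 8 and is an upper case. If drop-out were spread evenly over the 35 days, about 20% × 7/35 = 4% would be lost by Night 8.
- Night-to-night correlation ρ: 0.3 to 0.7. Correlation of each night with baseline, b: 0.3 to 0.5.
- Night 1 is observed and Night 8 is missing at random. The missing value is replaced by its prediction from arm, baseline and Night 1. Site is left out.

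**Formula.** The correlation between nights given baseline is r = (ρ − b²)/(1 − b²). Let h = (1 − r)/2. Relative to complete data:
- the variance that the ANCOVA reports is multiplied by 1 − m·h, because a predicted night adds no scatter of its own;
- the true variance of the treatment contrast is multiplied by 1 + h·m/(1 − m), because Night 8 was measured in only a fraction 1 − m.

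Reported SE / true SE = √[(1 − m·h) / (1 + h·m/(1 − m))]. The actual two-sided error is about 2Φ(−1.96 × ratio).

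**Extremes of the assumed range.**
- ρ = 0.7, b = 0.3: r = (0.70 − 0.09)/0.91 = 0.670, h = 0.165.
- ρ = 0.3, b = 0.5: r = (0.30 − 0.25)/0.75 = 0.067, h = 0.467.

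| m | h | Reported factor | True factor | SE ratio | Two-sided error |
|---|---|---|---|---|---|
| 4% | 0.165 | 0.993 | 1.007 | 0.993 | 0.052 |
| 4% | 0.467 | 0.981 | 1.019 | 0.981 | 0.054 |
| 5% | 0.165 | 0.992 | 1.009 | 0.992 | 0.052 |
| 5% | 0.467 | 0.977 | 1.025 | 0.976 | 0.056 |
| 10% | 0.165 | 0.984 | 1.018 | 0.983 | 0.054 |
| 10% | 0.467 | 0.953 | 1.052 | 0.952 | 0.062 |
| 20% | 0.165 | 0.967 | 1.041 | 0.964 | 0.059 |
| 20% | 0.467 | 0.907 | 1.117 | 0.901 | 0.077 |

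**Simulation.** Null simulations with three arms of 108 agree.
- One set put the standard error 0-1% too small at 4% missing, 2-5% at 10% and 3-10% at 20%, with two-sided error 0.046-0.052, 0.054-0.064 and 0.057-0.083.
- A second set, with 4,000 runs per setting, gave ratios of 0.97-1.00 at 5%, 0.96-0.98 at 10% and 0.92-0.94 at 20%. Its Monte Carlo error is about 0.0035 on the error rate and 0.011 on the ratio, so the results at 4-5% are barely separable from no effect.

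**Two comparisons.**
- If both nights are missing and the average is wholly predicted, the ratio is about 1 − m: 0.95 at 5% and 0.80 at 20%. The second set gave 0.95-0.97 and 0.79-0.81, with error up to 0.119.
- The primary rule uses a value that was really recorded: "then it will be imputed using the non-missing night value". In the second set it gave a ratio of 0.98-1.02 and an error of 0.044-0.055, which is nominal.

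**The case against.** The strongest reply is that the defect is partly inferred. The protocol does not say that one value is imputed, or that it is a bare prediction. Multiple imputation from a mixed model, analysed by the same ANCOVA and then combined, could be made to fit the words, and the SAP is the usual place to say so. This stands as a limit on certainty. It does not remove the point. MMRM is paired with BOCF, a single-value method, under one shared analysis sentence. Section 14.9.2.1 uses the idea of imputation only for single-value replacement. The same ANCOVA alone cannot yield a multiple-imputation standard error, so a SAP would have to add to this text.

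Three stronger readings are tempting, and the documents do not support them.
- **That the primary result is affected.** It is not. The analysis is optional, sits under an exploratory heading and decides nothing. The primary rule is well calibrated in the simulation.
- **That the check is worthless.** It is not. A sensitivity analysis first asks whether the estimate moves, and under missing at random the point estimate remains a usable comparison. Section 14.4 also repeats the efficacy analyses on the Per-Protocol set, exemplified by patients with all five PSG nights, who need no imputation.
- **That the error is large.** Missing rates above 20% exceed the protocol's entire drop-out allowance, and even 20% by Night 8 is extreme in a study running to Night 36. The both-nights case should be uncommon, since Night 1 PSG is recorded in clinic on the night of randomization and first dose. It is not impossible: the Full Analysis set asks only for some post-baseline PSG.

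**Conclusion.** The point holds in a limited form. Section 14.9.2.5 fixes a two-step procedure that, read naturally as single imputation, overstates the precision of an optional sensitivity analysis and tilts its p-value and interval toward significance.

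By the formula, the standard error is about 1-2% too small with 4-5% of patients missing Night 8, 2-5% with 10% and 4-10% with 20%. The corresponding two-sided error is 0.052-0.056, 0.054-0.062 and 0.059-0.077, and the simulated ranges are similar. At the lower, more plausible rates the effect is small. All of this rests on assumed missing rates and correlations, on missing at random, and on predictions that use arm, baseline and Night 1.

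It is worth correcting because the replacement is standard and nearly free, not because any conclusion of the trial depends on it.

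**What to change.** Remove MMRM from the list of imputation methods. State that the sensitivity analysis is an MMRM fitted to the observed Night 1 and Night 8 LPS, with treatment, night, treatment-by-night, baseline and pooled site, and an unstructured covariance. Report each dose-versus-placebo contrast averaged over the two nights, with the standard error from that model.

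If imputed data are wanted, use multiple imputation, run the same ANCOVA on each completed data set and combine the variances by Rubin's rules.

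The cost is a few lines of text. Section 14.1 lets the change be recorded in the SAP before database lock. The interval becomes slightly wider: at 10% missing by a factor of 1/0.983 = 1.02 to 1/0.952 = 1.05. Sample size, trial conduct and the primary analysis stay as they are.

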#### **14.9.2.6. Graphs of Efficacy**

Graphical representation (over time) for the primary efficacy parameter and other efficacy parameters of interest will be depicted.

### **14.10. Safety Data**

The primary assessment of safety will be based on the frequency of treatment-emergent adverse events and on the frequency of clinically notable abnormal vital signs and laboratory values.

#### **14.10.1. Adverse Events**

Adverse events will be recorded throughout the study and at early termination. Adverse events and medical conditions will be coded using the Medical Dictionary for Regulatory Activities (MedDRA) coding dictionary. Treatment-emergent adverse events will be defined as those events, which are newly occurring or worsening from baseline. In all cases only treatment emergent adverse events will be summarized.

Treatment-emergent adverse events will be summarized by treatment group, by presenting, for each treatment group, the number and percentage of patients having any treatment-emergent AE, having an AE in each body system, and having each individual AE. (Note: In any given category [e.g. body system] a patient will only be counted once.) Similar displays will be provided for prior (conditions ending prior to the first dose of study medication) and current conditions present while on study medication) medical conditions.

Adverse events will further be categorized by severity, relationship to study medication, and action taken. Other information collected will be listed, as appropriate. Any event starting more than 3 days after the final dose of study medication will be excluded from the above tables and only listed, unless the event caused discontinuation.

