##### **Day 37 and End-of-study Evaluations**

End-of-study procedures will be performed the morning of Day 37

- Full physical examination
- Full standard 12-lead ECG
- Vital signs (body temperature, respiratory rate, blood pressure, pulse, and weight)
- Laboratory evaluations (hematology, biochemistry and urinalysis)
- Serum pregnancy test for women of childbearing potential (WOCBP), except those who have been postmenopausal for at least 1 year or are surgically sterile
- BWSQ (prior to the battery of tests)
- Battery of tests (Post-sleep questionnaire, VAS, and DSST, in this order; one hour [ $\pm$  15 minutes] after awakening))
- Adverse events query
- Review of concomitant therapy
- IVRS call to report patient completion

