#### **12.2.4. Adverse Event Reporting Period**

Adverse events are to be recorded in the source documents from the time of the patient's informed consent signature until the end of the patient's study participation. Each adverse event, both serious and non-serious, will also be reported on the Adverse Events electronic CRF. CRF Completion Instructions will be provided to each investigational site. If the patient reports or the Investigator learns of a new AE(s) up to 7 days after the patient's last study visit or a new SAE(s) up to 30 days after the patient's last study visit, the investigational site personnel will ensure that these data are recorded on the Adverse Events electronic CRF for the study. The period during which an SAE must be reported may be extended if there is a strong suspicion that the event being reported is related to the study medication or a study procedure.

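### Events starting more than 3 days after the final dose are only listed, so a completer's late serious event or death enters no by-arm summary that the protocol describes

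*Protocol*

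**What the plan says.** Section 14.10 of the protocol rests the primary safety assessment on the frequency of treatment-emergent adverse events, together with notable vital signs and laboratory values. Section 14.10.1 defines treatment emergence as onset or worsening relative to baseline and gives no end date. It adds that "In all cases only treatment emergent adverse events will be summarized". It then sets a cut for its by-group displays: "Any event starting more than 3 days after the final dose of study medication will be excluded from the above tables and only listed". The sentence carries one exception: "and only listed, unless the event caused discontinuation". Serious events and deaths are not named as exceptions, and no separate table is described for them.

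Collection runs longer. Section 12.2.4 has the site record an event on the case report form if the patient reports it or the investigator "learns of a new AE(s) up to 7 days after the" last visit, or "a new SAE(s) up to 30 days after the" last visit for serious events. It allows the serious-event period to be extended when a link to treatment is strongly suspected. Section 12.2.3 uses the same two periods.

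The last scheduled visit is fixed in Section 10.2.2: "End-of-study procedures will be performed the morning of Day 37". The capsule given on Night 36 is wash-out placebo (Section 8.1), so the last double-blind capsule is taken on Night 35.

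**The concern.** The tabulation rule runs from the last dose and lasts 3 days. The collection rule runs from the last visit and lasts 7 or 30 days. An event can therefore meet the protocol's own definition of treatment emergence and be entered in the database, yet be kept out of the by-arm tables by its start date alone. For ordinary adverse events that is a common way to confine tables to the time near exposure. For deaths and serious events it means that the by-arm count is incomplete over a period in which the protocol deliberately collects them. An imbalance between arms in that period would show only to someone counting lines in a listing.

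A second, smaller problem is that Section 14.10.1 does not say which capsule is the final dose of study medication. Section 9.2 counts bottle 6, the wash-out placebo, among the study medication bottles, which points to Night 36. A reader who thinks of exposure to VEC-162 would take Night 35.

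**Working it through.** No sample size, power or alpha figure is involved, and the protocol states no figure for this gap, so there is nothing of its own to reproduce first. The check is day arithmetic on the nominal schedule.

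Inputs: last visit on Day 37 (Section 10.2.2); collection for 7 and 30 days after it (Section 12.2.4); table cut at 3 days after the final dose (Section 14.10.1); final dose on Night 36 or Night 35 (Sections 8.1 and 9.2).

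End of collection: adverse events 37 + 7 = Day 44; serious events 37 + 30 = Day 67. The follow-up days are Days 38 to 44 and Days 38 to 67.

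| Final dose | Tables stop | Adverse events only listed | Serious events only listed |
|---|---|---|---|
| Night 36 placebo | 36 + 3 = Day 39 | Days 40–44: 44 − 39 = 5 of 7 days | Days 40–67: 67 − 39 = 28 of 30 days |
| Night 35 double-blind | 35 + 3 = Day 38 | Days 39–44: 44 − 38 = 6 of 7 days | Days 39–67: 67 − 38 = 29 of 30 days |

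Visit 7 has a window of 2 days either way. It moves the last dose and the last visit together, so the counts do not change.

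**Wash-out period.** Day 37 is earlier than Day 38, so events on Night 36 and Day 37 are tabulated on both readings.

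**Discontinuation exception.** Section 7.3 defines discontinuation as leaving before all scheduled evaluations are done. For a completer those end on Day 37, so the exception can hardly apply to an event that starts on Day 39 or later.

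**Early terminators.** Let g be the days from last dose to termination visit, and take that visit as the last visit. The days covered by collection but not by the tables are (g + 7) − 3 = g + 4 for adverse events and (g + 30) − 3 = g + 27 for serious events. With g = 1 or g = 2 this returns the completer figures (5 and 28, or 6 and 29). Section 10.2.3 asks for the termination visit as soon as possible but sets no limit on g. Here the exception can apply, and it keeps in the tables the events that led to stopping.

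**The case against.** The strongest reply is that nothing here is inconsistent. A short treatment-emergent window is conventional, while longer collection serves safety reporting. Section 14.1 says that it describes the analyses in general terms, and the statistical analysis plan could add tables. Reporting after the last visit is also passive: no contact is scheduled after Day 37, so by-arm percentages for that period would rest on unsolicited reports. The two earlier sponsor studies summarised in Section 4.3 had no serious events, so late ones here may be few enough to read from a listing.

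Much of this stands. The 3-day tables are defensible, the two windows do not contradict each other, and counts will be small. What does not stand is that the matter is simply left to the analysis plan. The protocol settles where late events go, and it sends them to listings alone.

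Three stronger readings are tempting, and the documents do not support them.

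- A reader might infer that withdrawal is never compared between arms. Adverse events on Night 36 and Day 37 are inside the window. Rebound by polysomnography on Night 36 and the withdrawal questionnaire (Days 30 and 37) are secondary variables in Section 14.9.1.2, and Section 14.9.2.4 plans their analysis by treatment.
- A reader might infer that late events are discarded. They are listed, and those that caused discontinuation stay in the tables. Death is a recorded reason for discontinuation (Section 7.3), so a fatal event that ends participation is covered. A completer's later death is not.
- A reader might infer that everything found at a late termination visit is lost. The cut is on when the event starts, not on the visit date. Laboratory, vital-sign and ECG results are summarised under Sections 14.10.2 to 14.10.4, where no 3-day cut is stated.

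**Conclusion.** The concern holds in a limited form. For completers, the by-arm tables stop at Day 39 (or Day 38), while collection continues to Day 44 for adverse events and Day 67 for serious ones. A serious event or death starting in between enters no by-arm summary described in the protocol. The gap is 5 or 6 of the 7 follow-up days for adverse events and 28 or 29 of the 30 for serious events.

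These are calendar days, not events. The protocol gives no expected rate of late events, so no effect on a safety conclusion can be computed, and the number is likely to be small. The result assumes the nominal visit schedule and no analysis-plan table beyond those that the protocol describes. It bears on the completeness of the serious-event count by arm. It does not touch the planned assessment of rebound and withdrawal.

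**What to change.** 1. Keep the 3-day treatment-emergent tables.
2. State in Section 14.10.1 whether the final dose is the last double-blind capsule or the Night 36 placebo.
3. Exempt deaths and serious adverse events from the 3-day cut, and tabulate them by randomised arm over the full period in which they are collected.
4. Optionally, add one by-arm table of other adverse events that start after the cut and up to the end of collection, with a note that reporting after the last visit is passive and counts are expected to be small.

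The cost is one or two tables from data that are already collected, with no new visits or procedures. Section 14.1 allows changes to statistical methods to be documented in the analysis plan before database lock without a protocol amendment.
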